### 7.2.6 Contingency plans

At each clinical visit, the investigator (or delegate) will determine whether any AEs have occurred. Adverse events will be recorded in the AE page of the eCRF. If known, the medical diagnosis of an AE should be recorded in preference to the listing of individual signs and symptoms. The investigator must follow up on the course of an AE until resolution or stabilisation. If an AE is ongoing after the end of study visit, the AE will continue to be followed up until resolution or stabilisation.

If, during the study period, a participant presents with a pre-existing condition that was not noted at the time of study entry, the condition should be retrospectively recorded in the Medical History section of the eCRF. For SAEs occurring during the study, the investigator or delegate will enter all relevant information in the AE page of the eCRF. AEs due to this low risk study are not expected to occur; none were observed in the pilot study. Where study results suggest patterns of adverse events, study investigators will discuss concerns with clinical teams in a timely manner.

### 7.2.7 Student involvement

This study will form part of a PhD project for Associate Investigator [name], who is an Accredited Practising Dietitian enrolled at the University of Sydney. The student project will involve analysis of baseline data collected during the trial. We anticipate that other students will be involved in data collection, intervention delivery and data analysis at both sites.

## 7.3 Standard Care and Additional to Standard Care Procedures

| Standard Care Procedures               |                                         |               | Additional To Standard Care       |                                         |                                      |
|----------------------------------------|-----------------------------------------|---------------|-----------------------------------|-----------------------------------------|--------------------------------------|
| Procedure                              | Time/ Visit                             | Volume        | Procedure                         | Time/ Visit                             | Volume                               |
| Anthropometry                          | every visit                             |               | DXA                               | Baseline, weeks 16 and 52               |                                      |
| Bioelectrical impedance analysis (BIA) | Baseline, weeks 4, 16, 52 and 24 months |               | Psycho-behavioural questionnaires | Baseline, weeks 4, 16, 52 and 24 months |                                      |
| Biochemistry                           | Baseline, week 52 and 24 months         | 20ml of blood | Biochemistry                      | Week 16                                 | 20mL of blood                        |
| Blood pressure                         | Baseline, weeks 4, 16, 52 and 24 months |               | Biochemistry                      | Baseline, weeks 16 and 52               | 10mL of blood for storage (CHW only) |

|                  |                                                       |  |                      |                                                                  |  |
|------------------|-------------------------------------------------------|--|----------------------|------------------------------------------------------------------|--|
| Dietetic review* | Baseline, weeks 2, 4, 6, 9, 16, 26, 52, and 24 months |  | Dietetic review*     | Weeks 1, 3, 6, 12, 20, 36, SMS/email/phone support and 24 months |  |
| Clinical review  | Baseline and 16 week                                  |  | Psychologist Support | Baseline and as needed during 12 month study period              |  |

\* There is no single standard of care with these novel forms of dietary intervention. The indicated standard of care is based on current clinical practice at CHW.

## 7.4 Randomisation

After completion of screening visits, participants will be randomly allocated to one of the two intervention groups, using a computer-generated randomisation schedule (1:1) from the NHMRC Clinical Trials Centre (University of Sydney). Random allocation will occur via a process of minimisation with allocations concealed, and stratified by intervention site, age (13–14 years; 15–17 years), sex and body mass index (BMI) (equivalent to 30–34.9 kg/m^2; 35–45 kg/m^2). Forced allocation will be used for participants who have a family member enrolled in the study to keep family members within the same study arm. The Interactive Voice Response System (IVRS) at the NHMRC Clinical Trials Centre is able to force the allocation of a new participant based on a previously randomised participant (based on the ID number). These new participants will be included in the stratification tables used to randomise subsequent participants. Assessors for the primary outcome (BMI z-score at 52 weeks) and secondary outcomes will be blinded to treatment allocation.

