## **9.2 Power Calculations**

The Therapeutic Goods Administration (TGA) defines successful weight loss as at least a 5% decrease in initial bodyweight in adults. This is approximately equivalent to a 0.12 decrease in BMI z-score in adolescents. This intervention will be considered successful if there is a 5% difference between groups at 52 weeks as defined by the TGA [61].

Assuming a BMI z-score difference at 52 weeks of 0.12 and a SD 0.24 (based on our previous RCT of age and weight matched participants [61]; 80% power, and a two-sided significance level of 0.05, a sample size of 65 adolescents per group, 130 in total, is required. As indicated above we anticipate a 30% attrition rate and we will recruit 186 adolescents.

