## **9.3 Statistical Methods to Be Undertaken**

Data analyses will be carried out according to a pre-established plan, with the primary analysis based on intention to treat and with statistical support from the Biostatistician in the Office of Research, CHW. Analysis will be undertaken blinded. The difference in BMI z-score between groups at 52 weeks will be assessed using a t-test. Mixed models will also be used to investigate changes over time. The mixed models procedure will take into account within participant correlations and missing data points. A time by group interaction will be included to investigate whether rates of change of weight loss were significantly different between the two study groups. A/[name] along with SCHN statistician [name] will oversee the statistical analyses.

Post hoc analysis will compare protocol adherers to non-adherers. An adherer will be defined as an individual who attends at least half of their scheduled appointments across the 12 month study period (either face to face or electronic). Additionally, at 52 weeks in measurement of the primary outcome (BMI z-score), a variation of plus or minus 4 weeks (i.e. measurement between 48 and 56 weeks) will be considered within protocol.

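### Family members are forced into one arm, but the named 52-week t-test has no term for family and the concealment statement fails for relatives who enrol later

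*Protocol*

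**What the plan says.** Section 7.4 allocates 1:1 by minimisation on site, age, sex and BMI, and describes the allocations as concealed. It then makes an exception: "Forced allocation will be used for participants who have a family member enrolled in the study". The allocation system copies the arm of the relative already randomised, identified by ID number, and "These new participants will be included in the stratification tables used to randomise subsequent participants". The concealment statement carries no matching exception.

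Section 7.2.1 says participants learn their diet during phase 1, the first four weeks. Recruitment is expected to last about 18 months (sections 7.2.5 and 9.1).

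Section 9.3 gives the test: "The difference in BMI z-score between groups at 52 weeks will be assessed using a t-test". The mixed model described next handles correlation within a participant and missing data; family is not mentioned. Section 9.2 sizes the trial as if all participants were independent: "Assuming a BMI z-score difference at 52 weeks of 0.12 and a SD 0.24", and "80% power, and a two-sided significance level of 0.05, a sample size of 65 adolescents per group, 130 in total, is required".

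**The concern.** Two things follow from forced allocation.

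The first is dependence. Relatives share genes, a household and, by design, a diet arm, so their 52-week BMI z-scores are likely to be positively correlated. When positively correlated people always sit in the same arm, the variance of the difference in means exceeds what a t-test estimates. The design creates this dependence, and section 9.3 names a test and a correlation structure that both omit it.

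The second is concealment. A later relative's arm is fixed before that person is screened. Under section 7.2.2 a parent usually attends the dietitian sessions, and under section 7.10 the parent gives consent. Once the first child knows the diet, the person consenting for the second child can know that child's arm in advance. Under section 7.10 a dietitian may also give the study information to the family. This opens a route to selection by arm.

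**Working it through.** **The plan's own figure.** Inputs from section 9.2: difference 0.12, SD 0.24, two-sided alpha 0.05, power 80%.

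- n per group = 2 × (1.960 + 0.842)² × 0.24² / 0.12² = 62.8, so 63; the t-based value is 63.8, so 64. The stated 65 agrees.
- Power at 65 per group is 81.3% (normal) or 80.8% (t).
- Recruitment: 130 / 0.70 = 185.7, so 186, as stated.

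There is little slack above 80%.

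**Family clustering alone.** Two inputs are assumed because the protocol does not give them: the number of same-arm pairs among the 186 recruited, and the within-family correlation ρ of the outcome. With f the share of participants who belong to a pair:

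- f = 2 × pairs / 186
- design effect DE = 1 + f × ρ
- type I error of the uncorrected t-test ≈ 2 × Φ(−1.96 / √DE)
- power of a correctly clustered test: t-based, with 65 / DE per group

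| Pairs (assumed) | ρ (assumed) | f | DE | Type I error, plain t-test | Power, clustered test |
|---|---|---|---|---|---|
| 5 | 0.3 | 10/186 = 0.054 | 1.016 | 5.2% | 80.1% |
| 18 | 0.5 | 36/186 = 0.194 | 1.097 | 6.1% | about 77% |

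The last two columns belong to different tests. At DE 1.097 the uncorrected t-test keeps about 80% power; the fall to 77% appears only once clustering is handled.

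**Attrition.** The table uses recruited pairs. If the 30% attrition is independent within families (assumed), a completer's relative also completes with probability 0.7. The upper case becomes f = 0.194 × 0.7 = 0.135, DE = 1.068 and type I error 5.8%. If relatives drop out together, there is no reduction.

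**The opposing effect.** Minimisation balances prognostic factors, and an unadjusted t-test does not use that balance, so its standard error is too large. As a rough guide, the two effects cancel when the factors explain a share f × ρ of outcome variance. Both were simulated together (130 participants, 6,000 runs per scenario):

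| Allocation | Variance explained by factors (assumed) | True SE / t-test SE, f 10%, ρ 0.3 | True SE / t-test SE, f 20%, ρ 0.5 |
|---|---|---|---|
| Simple randomisation | none | 1.01 | 1.04 |
| Minimisation | 10% | 0.97 | 1.02 |
| Minimisation | 30% | 0.87 | 0.91 |

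A ratio above 1 means that the t-test's standard error is too small. In the last row type I error was 2.4% and 2.9%, below the nominal 5%.

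**Concealment.** This part needs no arithmetic. Section 7.4 claims concealment without exception and also fixes a later relative's arm in advance; section 7.2.1 discloses the arm to the first member within four weeks; enrolment runs for about 18 months. The claim cannot hold for a relative who enters after that disclosure.

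**The case against.** A reader might infer that the planned confidence interval is too narrow and that the trial's type I error exceeds 5%. The documents do not support that. The number of families is unknown and may be very small, and the balancing factors include baseline BMI, which may well predict BMI z-score at 52 weeks. With a modest share of variance explained, the t-test is about right; with a larger share it is conservative. This objection stands, and it limits the claim to the clustering component. It does not make the t-test sound: two unhandled errors of opposite sign cancel only by chance, and once the analysis adjusts for the minimisation factors the offset goes and the family correlation remains.

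A reader might also infer that every forced allocation is known in advance, or that families choose by diet. Relatives who screen and enrol together need not know the arm, the protocol does not say how often relatives enrol later, and nothing shows that selection occurs. Nor are relatives exempt from screening: section 7.9 requires it for all participants before enrolment. Entering relatives in the stratification tables is ordinary bookkeeping and no defect.

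Finally, section 9.3 refers to a pre-established analysis plan that is not shown and may include a family term. That is a fair caution, but the protocol itself names an unadjusted t-test and limits the mixed model's correlation to the participant.

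**Conclusion.** The point holds in a limited form. The protocol's named analysis ignores a dependence that its own allocation rule creates. The family component is small: a standard error about 1% to 5% too low (√1.016 = 1.008; √1.097 = 1.047), on assumed figures of 5 to 18 pairs and correlation 0.3 to 0.5, before attrition. Whether the t-test is anti-conservative or conservative overall cannot be determined from the document.

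The concealment statement is wrong for relatives who enrol after the first member has been told the diet, and only for them. This conclusion rests on no assumed figure, though how many participants it affects is unknown.

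**What to change.** **Section 9.3.** Make the primary comparison a model adjusted for the minimisation factors (site, age, sex, baseline BMI), with family-clustered standard errors or a family random effect. Add a sensitivity analysis that keeps only the first-randomised member of each family. Report the number of forced allocations by arm.

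**Section 7.4.** State that the allocation of a relative who enrols later by forced allocation is not concealed.

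Families stay in one arm. The system already links relatives by ID number, so no new data are needed. The cost is a little extra analysis and possibly a marginally wider interval from the family term; adjustment for the minimisation factors works in the other direction.

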### 6.3.2 Secondary Outcome

The following outcome measures performed at week 16 and 52, and at 24-months follow-up will be used to answer study questions

| Outcome Measures                     | Applicable At:
The Children's Hospital At Westmead
Monash Children's Hospital
Monash University                                                                                                                 | Applicable Only At:
Monash Children's Hospital Monash
University                                                                                                                                                                                                                                                                                       |
|--------------------------------------|--------------------------------------------------------------------------------------------------------------------------------------------------------------------------------------------------------------------------|--------------------------------------------------------------------------------------------------------------------------------------------------------------------------------------------------------------------------------------------------------------------------------------------------------------------------------------------------------------|
| Body composition              | Weight
BMI as a % of the 95th centile for age
Waist-to-height ratio
Fat mass                                                                                                                                    |                                                                                                                                                                                                                                                                                                                                                              |

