| Diet                          | Diet quality
Food Choices
Food Patterns
Diet acceptability (Week 16 & 52 only)                                                                                                                                  |                                                                                                                                                                                                                                                                                                                                                              |
| Cardio-metabolic risk factors | Systolic and diastolic blood pressure
Serum biochemistry (high-sensitivity CRP)
Lipid profile (total triglycerides, high-density and low-density cholesterol)
Glucose
Insulin
Liver function tests (LFTs) |                                                                                                                                                                                                                                                                                                                                                              |
| Inflammatory markers          |                                                                                                                                                                                                                          | (Week 16 & 52 only) Adipokines [Adiponectin, Leptin, Monocyte chemotactic protein-1 (MCP-1), Plasminogen activator inhibitor-1 (PAI-1) (Total) and Tumour necrosis factor-alpha (TNF-α)]
Cytokines [Interleukin-1 beta (IL-1β), Interleukin-6 (IL-6) and Interleukin-8 (IL-8)]
Hepatocyte growth factor (HGF)
Nerve growth factor (NGF)
Resistin |
| Psycho-behavioural            | Body dissatisfaction
Bulimic eating episodes
Psychological wellbeing
Weight related quality of life
Emotional wellbeing
External eating habits
Depression
Anxiety
Stress                         |                                                                                                                                                                                                                                                                                                                                                              |

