## 7.2 Study Type & Design & Schedule

### 7.2.1 Study Design

This is a prospective, randomised, multi-centre study designed to determine if IER results in lower BMI z-score after 52 weeks of intervention in adolescents with obesity, compared with a standard, usual care, hypocaloric dietary intervention. A total of 186 participants aged 13–17 years will be randomised on a 1:1 ratio to 4 weeks of VLED, followed by 48 weeks of IER (experimental arm), or 4 weeks of VLED, followed by 48 weeks of current best-practice calorie restricted diet (active control arm). To ensure even distribution, randomization will be stratified by clinical study site, age, sex and BMI. Randomisation will occur at baseline and participants will be informed of their allocated dietary patterns during phase 1.

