d Weight should be measured to the nearest 0.1kg by a blinded trained assessor on the electronic scales at each visit. At 24-months, participants will be asked to self-report their weight in an online questionnaire; those who attend an on-site appointment will also have their weight measured.

e Height should be measured to the nearest 0.1cm by a blinded trained assessor using a stadiometer at each visit. At 24-months, participants will be asked to self-report their height in an online questionnaire; those who attend an on-site appointment will also have their height measured.

f Waist circumference should be measured by a blinded trained assessor using a flexible steel tape measure to the nearest 0.1cm at the horizontal distance around the umbilicus using the left hand under technique.

g BIA should be measured by a blinded trained assessor on a Tanita MC780MA body composition analyser at The Children’s Hospital at Westmead and Seca 515 scales at BASE at Monash University at each visit.

h DXA should be measured by a trained assessor on the Prodigy, Lunar-GE DXA at the Children’s Hospital at Westmead site, and the GEiDXA at the Monash site.

i All questionnaires will be completed by participants on an iPad during the study visit. Details pertaining to each questionnaire can be found in Section 7.5 and attachments in the Appendix.

j Blood pressure should be measured by a blinded trained assessor using an automated monitor under standardized conditions.

k For these “standard blood tests”, a 20ml fasting blood sample will be collected by a blinded trained assessor using standard operating procedures. Blood samples will be stored in a secure -80°C freezer at the Monash site and then samples batched and processed later. At The Children’s Hospital at Westmead site the blood samples will be transferred to CHW Pathology for immediate processing.

l Ketones will be measured weekly during weeks 1-4 using blood from a finger prick using the Freestyle Optium Neo Blood Glucose and Ketone Monitoring System. Ketones will also be measured at week 16 and 52 for those in the IER group, using the Freestyle Optium Neo.

m Participants will be asked to complete the ASA24-Australia online dietary assessment tool prior to attending visits at baseline, week 12 and week 36 or will otherwise complete this on an iPad at the study site.

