The EDE-Q will be used as a screening tool at baseline to identify participants with an undiagnosed eating disorder requiring treatment prior to participation in a weight management study. Participant will be assessed and referred as per standard clinical practice.

The CESDR-10 will be used as a screening tool at baseline to identify participants at high risk of clinical depression requiring referral for further assessment.

- 5. Dietary assessment:** Diet quality, food choices and food patterns will be assessed using the Australian Child and Adolescent Eating Survey (ACAES)[48, 49], a validated self-administered, semi-quantitative food frequency questionnaire, which takes ~15 minutes to complete and provides immediate analysis of the results and comparison of food and nutrient intake with nutrition targets. Participants will complete the survey at baseline, week 16, week 52 and at 24-month follow-up. They will be sent a personalized link to the tool. Participants may complete the survey at home or on an iPad at their dietitian visits.
- 6. Sedentary behaviour, physical activity and sleep quality:** will be assessed using validated tools appropriate for this age group. The questionnaires will be completed on an iPad using RedCap software. The questionnaires that will be used are:
- Godin Leisure-time Questionnaire [50]
  - Pittsburgh Sleep Quality Index [51]
- 7. Blood pressure:** Systolic and diastolic blood pressure will be measured using an automated monitor under standardised conditions by trained study personnel blinded to treatment allocation.
- 8. Biochemistry:** A 20 mL fasting blood sample will be collected to measure high-sensitivity CRP, lipids (total triglycerides and high-density and low-density cholesterol), glucose and insulin levels, and liver function. As poor renal function is a contraindication for initiating a VLED plan,

urea and electrolytes (UEC) will be measured at baseline. All blood samples will be collected by trained personnel using standard operating procedures. The Children's Hospital at Westmead will also store a 10mL sample of blood for later analyses of a range of known (e.g. gut hormones and peptides (leptin and ghrelin) and metabolomics) and unknown (novel) biomarkers related to obesity and cardio-metabolic risk. These blood samples will be stored at Westmead Biobank. BASE at Monash University will store 2mL of the 20mL fasting blood samples as serum for later analyses of hormones and metabolites related to obesity.

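### Section 7.4 states assessor blinding for all secondary outcomes, but 16 of the 30 all-site ones are self-reported by participants who know their diet

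*Protocol*

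**What the plan says.** Section 7.4 (Randomisation): "Assessors for the primary outcome (BMI z-score at 52 weeks) and secondary outcomes will be blinded to treatment allocation". The sentence names the secondary outcomes as a whole and sets none apart.

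Section 7.2.1 (Study Design): "participants will be informed of their allocated dietary patterns during phase 1". Phase 1 covers up to the first four weeks, so participants know their diet before the week 16, week 52 and 24-month assessments that section 6.3.2 names for the secondary outcomes.

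Section 7.5, item 5, on the diet survey, a self-administered food frequency questionnaire: "Participants may complete the survey at home or on an iPad at their dietitian visits". Table 2 footnote i, which is attached to the diet assessment as well as to the psychological, activity and sleep questionnaires, says instead that participants complete all questionnaires on an iPad at the study visit. Section 7.5, item 12, takes acceptability from participant questionnaires.

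For most staff-measured items the Table 2 footnotes do specify a blinded assessor: weight, height, waist, bioelectrical impedance, blood pressure and the standard blood sample.

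**The concern.** When a participant fills in a questionnaire, the participant is the assessor. A participant told their diet in phase 1 is not blinded, so the protection stated in 7.4 does not exist for those outcomes.

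The affected outcomes matter to the trial's purpose. Section 5.1 sets out to test whether intermittent energy restriction is effective, safe and acceptable to adolescents, and section 5.2 names disordered eating as a potential safety concern. Eating behaviour, mood, quality of life and acceptability are all measured by self-report, and such answers can be coloured by expectation. If the 7.4 sentence were carried unchanged into a report, a reader would give these results more weight than the design supports.

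The setting adds to this for one instrument. The study dietitian supplies the meal plan and encourages adherence to it (section 7.2.2, Phases 2 and 3). A survey of what the participant eats, completed at that dietitian's visit, invites answers that match the plan.

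**Working it through.** The protocol gives no count of self-reported outcomes, so there is no stated figure to reproduce. The count below uses the outcome table in section 6.3.2, with each outcome classed by its method in section 7.5 and the Table 2 footnotes.

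**All-site column, item by item**

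| Group | Items | Self-reported |
|---|---|---|
| Body composition ("Weight BMI as a % of the 95th centile for age Waist-to-height ratio Fat mass") | 4 | 0 |
| Diet ("Diet quality Food Choices Food Patterns Diet acceptability (Week 16 & 52 only") | 4 | 4 |
| Cardio-metabolic | 9 | 0 |
| Psycho-behavioural | 9 | 9 |
| Lifestyle (3 questionnaires, 1 activity monitor) | 4 | 3 |
| Total | 30 | 16 |

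The cardio-metabolic count of 9 takes blood pressure as 2, CRP as 1, the lipid line ("Lipid profile (total triglycerides, high-density and low-density cholesterol") as 3, and glucose, insulin and liver function as 1 each: 2 + 1 + 3 + 1 + 1 + 1 = 9.

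- Total: 4 + 4 + 9 + 9 + 4 = 30.
- Self-reported: 4 + 9 + 3 = 16.
- Share: 16/30 = 53.3%.

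**How far the share depends on counting**

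- By listed line (blood pressure 1, lipids 1): 4 + 4 + 6 + 9 + 4 = 27, so 16/27 = 59.3%.
- Blood pressure 2, lipids 1: 16/28 = 57.1%. Blood pressure 1, lipids 3: 16/29 = 55.2%.
- If diet acceptability were not classed as self-report but kept in the 30: 15/30 = 50.0%. Section 7.5, item 12, makes it participant questionnaire data, so 16 is the better count.

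**Adding the Monash-only column**

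- Inflammatory markers: 5 adipokines + 3 cytokines + hepatocyte growth factor + nerve growth factor + resistin = 11.
- Resting energy expenditure 1, hunger 1, satiety 1, gene expression 1: 11 + 4 = 15 items, of which 2 (hunger and satiety) are self-reported.
- Total: 30 + 15 = 45. Self-reported: 16 + 2 = 18. Share: 18/45 = 40.0%.

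**Setting of completion**

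Section 7.5, item 5, allows the diet survey at home or at dietitian visits. Footnote i places it at the study visit. Neither passage says that completion comes before the consult or apart from it. The dietitian's visit is named expressly only for this survey, which yields diet quality, food choices and food patterns: 3 of the 16 outcomes.

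**Primary outcome**

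BMI z-score at 52 weeks comes from weight and height, which section 7.5, item 1, and footnotes d and e assign to a blinded trained assessor. It is outside this point.

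**The case against.** The strongest reply is that the protocol uses the word assessor for staff who take measurements. On that reading 7.4 says nothing about participants, and the protocol hides nothing: it states openly that participants learn their diet and complete the questionnaires themselves. Participants in a diet trial have to know their diet, and self-report is the usual way to measure these constructs. Both arms receive active diets on the same contact schedule, so any wish to please the dietitian acts in both, and the direction of a bias is conjecture. Safety does not rest on questionnaires alone, since adverse events are elicited at each visit and an oversight committee reviews serious events.

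Much of this stands. The questionnaires are not at fault, and the direction and size of any bias are unknown. But 7.4 is not limited to staff-measured outcomes, and the narrow reading is best secured by writing it in.

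Three stronger readings are tempting, and the documents do not support them.

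- A reader might infer that more than half of all secondary results lack blinding. That holds only for the all-site column; with the Monash-only items the share is 40%.
- A reader might infer that fat mass is measured unblinded, because Table 2 footnote h says only that "DXA should be measured by a trained assessor on the Prodigy". But the general sentence in 7.4 covers fat mass. The word is also missing elsewhere: in footnotes n and p, and in section 7.5 for impedance and bloods, although footnotes g and k include it for those two. Its absence in one place is not evidence of unblinded measurement.
- A reader might infer mixed roles from section 7.2.7: "We anticipate that other students will be involved in data collection, intervention delivery and data analysis at both sites". This speaks of several students across two sites and does not say that one student holds several roles. Section 7.4 requires blinded assessors, section 9.3 a blinded analysis, and section 11.1 coded, de-identified data before analysis.

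**Conclusion.** The blinding statement in section 7.4 is too broad. It cannot hold for 16 of the 30 all-site secondary outcomes (53%), or about 18 of 45 (40%) when the Monash-only items are included. The primary outcome is not affected. Separately, sections 7.5 and Table 2 footnote i disagree on where the diet survey is completed, and the former allows it at the treating dietitian's visit; this concerns 3 outcomes.

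The counts assume that blood pressure is two outcomes, that lipids are three, that the activity monitor is not self-report, and that diet acceptability is. Weight and height at 24 months, which footnotes d and e also take by self-report, are not counted. The conclusion that a large share of secondary outcomes is outside the stated protection does not depend on these choices. The documents give no basis for the size or direction of any reporting bias. The point is an overstated design property and a loosely fixed setting, not a demonstrated bias.

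**What to change.** 1. In section 7.4, limit the blinding statement to staff-measured and laboratory outcomes. Add that questionnaire outcomes are self-reported by participants aware of their allocation and will be interpreted as open-label.
2. Reconcile section 7.5, item 5, with Table 2 footnote i. Have the outcome questionnaires at weeks 4, 16 and 52 completed by link or iPad before, and away from, the dietitian consult. Leave the existing safety review of screening and monitoring surveys unchanged.

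The first change is wording only. The second costs a fixed order of activities at those three visits; electronic self-completion is already planned, so only the order and the separation are new.
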